## **Measures**

*Primary Outcome Measures:* The primary outcome measure will be 30-day point prevalence abstinence at 6 months post-intervention. This was also the primary outcome measure in our original trial and is a recommended outcome variable for tobacco cessation trials. Continued use of the same outcome variable allows us to merge the two datasets to allow an urban comparison group for the proposed trial.

*Content of baseline survey:* All items have been employed by us in previous studies, including our earlier RCT of mailed NRT in a largely urban sample. Participants will be asked: a) number of cigarettes smoked per day; b) level of nicotine dependence using the revised Fagerstrom test for nicotine dependence (Test-retest reliability = .78-.84); c) number and duration of past quit attempts; d) past use of NRT and other anti-smoking medications; e) use of stop smoking services; f) intent to quit smoking in the next 6 months and 30 days; g) quantity and frequency of alcohol consumption; h) illicit drug consumption (ever and past year); and i) a series of demographic characteristics. Items assessing the inclusion criterion of interest in receiving nicotine patches will be nested within items assessing use of stop smoking medications. In addition, as smoking impacts on health-related quality of life (HRQoL), the HRQoL will be additionally measured in all responders using the EUROHIS-QOL, an 8-item version of the World Health Organization HRQoL measure. Finally, questions about general health status will be asked which will include questions about health contraindications for NRT use.

*Content of 6-month post-intervention follow-up survey:* Participants will be asked their current smoking status, including length of time without smoking in order to assess the primary outcome variable. Participants who have not quit will be asked how many cigarettes per day they currently smoke and their intentions to quit smoking; how soon after waking they smoke their first cigarette; and if, since their baseline interview, they have stopped smoking for even one day because they were trying to quit. Participants in the experimental group will be asked if they received free NRT and, if they did, to evaluate their experiences with NRT and to elaborate on their efforts to quit smoking. These questions will include items asking whether the participants used the NRT (none, some, all) and what they did with the NRT that they did not use themselves. These questions will be asked after the core smoking status outcome measures have been assessed. Participants in the control group will also be asked about their use of NRT but the questions will be framed to reflect purchase of NRT from sources other than this ongoing study.

Participants in both conditions will also be asked about their use of other smoking cessation aids and services, including electronic cigarettes, self-help/online methods, as well as participation and/or receipt of various forms of advice and counselling from family physicians, smoking cessation specialists, or other healthcare providers. As some individuals are known to initiate use of other tobacco products after stopping use of conventional cigarettes, such as cigars or non-combustible products such as smokeless tobacco or electronic cigarettes, participants who report smoking abstinence will be asked if they currently use other tobacco or nicotine containing products. This will allow us to examine whether people who quit cigarettes compensate with other forms of nicotine delivery.

*Municipal characteristics:* Relevant municipal characteristics for the proposed analyses can be generated from the most recently available Canadian Community Health Survey (CCHS) data sets (average smoking rate, region, population density, average SES) and will be merged with the baseline and follow-up data collected as part of this trial. Health services availability will be generated based on publicly available data on number of MDs by location, as well as other public health services locations. The approach will be similar to that outlined by McEachern et al. (2016). For the proposed trial, we will employ the database of Desktop Mapping Technologies Inc. (DMTI). Enhanced Points of Interest (EPOI) is a vector GIS database of over 1 million business and recreational points of interest for all provinces/ territories in Canada (e.g., health care facilities, tobacco retailers, pharmacies). Data linkage to the participating municipalities will be consistent with linkage approaches used in previous research where geocodes for the relevant businesses are located in each municipal buffer (i.e., bounded areas for each municipality in which the different built environment characteristics are quantified). Distance between participants' location and the closest health services available will be recorded.

**Power calculations:** The power calculation was conducted to estimate the sample size needed to test the primary hypothesis that participants receiving the NRT package will display significantly greater quit rates (30 day abstinence) at 6-month follow-up as compared to those not offered the NRT package. Our secondary analysis of the rural participants in our earlier trial indicated a large effect (OR = 9.59; 8.9% 30-day abstinence rate at 6 months in those receiving NRT vs 1% in those not receiving the intervention). However, this estimate is not stable due to the small sample size (n = 200 in participants from rural regions; 95% CI 1.19 to 77.16). As such, we have reduced the anticipated size of the impact of the intervention to 75% to generate the sample size estimate for the current proposal (i.e., OR = 7.1; 6.7% 30-day abstinence rate at 6 months in those receiving NRT vs 1% in those not receiving the intervention). This will allow for the likely possibility that, while the impact of the NRT intervention is large in rural regions, it may not be as large as was observed in the secondary analyses. The power analysis was based on Monte Carlo simulations. Randomly distributed dropouts were also included in the simulations, at a rate of 20%; thus accounting for the 20% attrition expected between baseline and 6-month post-intervention follow-up based on earlier trial findings. Quitting smoking was the binary outcome, measured as 30-days abstinence. A sample of 290 participants per group (intervention versus control) is needed in order to obtain 80% power with 95% confidence interval. Further, analyses from our earlier trial established that 50.1% of participants from rural regions would be interested in receiving nicotine patches (and would use it within a week to quit), leading to a baseline survey needed of 1,138 participants. Finally, results from our earlier trial found that 10% of those recruited at baseline were not eligible because of reporting a health condition

contraindicating NRT use without the supervision of a doctor. Thus, in order to conduct this trial, we would need to recruit 1,252 participants for the baseline survey in order to have sufficient participants for the trial (1,138 X 110%).

**Analysis Plan:** Multilevel logistic modelling will be employed. The analyses are staged, with tests of the primary hypothesis (impact of the NRT intervention on 30-day abstinence rates at 6 months) as the first step and with step 2 involving tests of municipal- and individual-level factors predicted to explain the anticipated large impact of the NRT intervention in rural settings.

**Step 1:** Tests whether the provision of the NRT intervention impacts on 30-day abstinence rates. Experimental condition (participant randomly assigned to receive the NRT intervention package or to the control condition) is the categorical predictor in these analyses. Participants lost to follow-up will be assumed to be current smokers. As part of the step 1 analyses, we will also conduct a chi-square test to explore whether there is differential loss to follow-up between experimental conditions. Further we will replicate these analyses with all subjects with missing data excluded from the analyses. If the results are the same between the analyses where the missing data is excluded and where subjects lost to follow-up are assumed to still be current smokers, then we can safely assume that there is no differential attrition between conditions (or, at least none that impacted on the outcome of the trial). Finally, these analyses will be replicated with only those participants who provide *biochemically validation* of abstinence are coded as achieving abstinence at 6-month follow-up (all other participants are assumed to be current smokers).

**Step 2:** Tests to identify factors that systematically vary between individuals, and between municipalities, that explain the size of the impact of the NRT intervention on self-reported 30-day abstinence at 6-month follow-up. For these analyses, the data from urban comparison sample will be combined with the data collected in the current project of rural participants in order to allow for stronger tests. We have *pre-specified two hypothesized municipal factors* and predict that prevalence of smoking at the municipal level, and availability of health services in the municipality, will be related to the size of the impact of the NRT intervention. The multi-level logistic regression models constructed will include municipal-level sampling frame data (province or territory region of Canada), and municipal level smoking prevalence and health services availability data to determine the size of the impact of the intervention with the individual-level outcome data. Individual demographic (including participant gender) and severity of smoking characteristics will be included in order to identify individual-level factors relevant to the impact of the intervention.

*Secondary analyses* will add other characteristics of the municipality [average SES, population density, tobacco retailer density, NRT distributor (e.g., pharmacy, grocery store) density] to identify other contextual factors that may be important in determining the size of the impact of the NRT intervention. Additional secondary analyses will assess the effects of NRT and other predictors on relevant dependent measures pertaining to those who have not quit. These analyses will include multilevel models predicting the number of cigarettes smoked, intentions to quit, and whether participants have quit temporarily during a given time-period.

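### The other-nicotine question cannot separate new use from continued use, because it goes only to abstainers at 6 months and no baseline counterpart is listed

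*Protocol*

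**What the plan says.** All of this is in the Protocol, section Measures.

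- **Motive for the item** (6-month follow-up survey): "some individuals are known to initiate use of other tobacco products after stopping use of conventional cigarettes".
- **The item itself:** "participants who report smoking abstinence will be asked if they currently use other tobacco or nicotine containing products".
- **What it is meant to deliver:** "This will allow us to examine whether people who quit cigarettes compensate with other forms of nicotine delivery".
- **Related follow-up questions, not limited to quitters:** "Participants in both conditions will also be asked about their use of other smoking cessation aids and services, including electronic cigarettes", and "Participants in the control group will also be asked about their use of NRT". For controls the NRT question concerns supplies obtained outside the study. The experimental group is asked about the patches it was sent.
- **Baseline survey:** the listed topics a) to i) begin with "number of cigarettes smoked per day". The entries closest to other nicotine products are "d) past use of NRT and other anti-smoking medications; e) use of stop smoking services". The remaining topics are dependence, quit attempts, intention to quit, alcohol, illicit drugs and demographics, followed by quality of life and general health. Other tobacco products and e-cigarettes are not listed.

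**The concern.** The Protocol's own motive for the item is that people take up another product after giving up cigarettes. To see that, one needs to know what the person used before quitting, and preferably what people who kept smoking use now. The current-use question supplies neither.

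Eligibility rests on smoking at least 10 cigarettes a day and does not exclude people who already use another product. Such people can enter the trial without being identified. Someone who smoked and vaped at baseline, then stopped cigarettes and vaped exactly as before, gives the same answer at 6 months as someone who took up vaping in order to quit.

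At stake is a descriptive statement on substitution that the data could not support. A baseline value that was never collected cannot be recovered in the analysis.

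**Working it through.** **1. The plan's own figure, for context.** The power calculation gives 290 per group for 80% power, with 6.7% against 1% abstinent and 20% attrition. Completers per group: 290 × 0.8 = 232. Exact enumeration of the two-sided Wald test of the log odds ratio gives 81.0% power with 232 completers per group. With 290 per group and missing counted as smoking it gives 80.9%. The stated figure is reproduced, and nothing below alters it.

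**2. What is recorded, by product.**

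| Product | Baseline | 6 months, abstainers | 6 months, continuing smokers |
|---|---|---|---|
| Cigars, smokeless tobacco | none listed | current use | none listed |
| E-cigarettes | none listed | current use, and use as a cessation aid | use as a cessation aid only |
| NRT | past use | current use (as a nicotine product), and NRT questions worded by arm | NRT questions worded by arm |

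No row has current use at both times. No row has current use for both abstainers and continuing smokers.

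**3. Why one follow-up value is not enough.** Let *u* be the share of abstainers who already used another product and still do, and *s* the share of the others who started. The item then shows

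observed use = *u* + (1 − *u*) × *s*.

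The documents give no value for *u*, so 10% to 30% is an assumption.

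| *u* | *s* = 0 | *s* = 10% |
|---|---|---|
| 10% | 10% | 0.10 + 0.90 × 0.10 = 19% |
| 20% | 20% | 0.20 + 0.80 × 0.10 = 28% |
| 30% | 30% | 0.30 + 0.70 × 0.10 = 37% |

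An observed 10% can mean that nobody started (*u* = 10%, *s* = 0) or that every user did (*u* = 0, *s* = 10%). One equation cannot fix two unknowns. An increase in existing use is also invisible, since the item as described asks only whether the person uses such products now.

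**4. How many would be asked.**
- Rates applied to all randomised: 290 × 0.067 = 19.4 and 290 × 0.01 = 2.9, together about 22.
- Rates applied to the 80% followed up: 19.4 × 0.8 = 15.5 and 2.9 × 0.8 = 2.3, together about 18.
- Followed up in total: 580 × 0.8 = 464. So 464 − 22 = 442 to 464 − 18 = 446 would not get the current-use item.

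These counts use the 30-day abstinence rates. The item goes to anyone who reports abstinence, with no 30-day limit stated, so the number asked could be larger.

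**5. Precision.** If 4 of 20 abstainers used another product (20%), the exact 95% confidence interval would run from about 6% to 44%.

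**The case against.** The strongest case against the point has four parts.

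- **It is peripheral.** Compensation appears in one sentence of a survey description. It is not in the research questions, the hypotheses, the primary outcome or the Analysis Plan, whose additional secondary measures concern people who have not quit. This stands, and it limits the weight of the point. It does not make the sentence correct.
- **There is some comparison and some baseline information.** A reader might infer that nobody but abstainers is asked about other nicotine, that the arms cannot be compared at all, or that baseline is blank. The documents do not support that. E-cigarettes as a cessation aid and NRT are asked in both arms whether or not the person quit, and "past use of NRT and other anti-smoking medications" is a baseline topic. But use as an aid is not current use, past use is not concurrent use, and neither covers cigars or smokeless tobacco. The baseline list also gives topics rather than the questionnaire, so the absence of an e-cigarette question is an inference from that list.
- **Misreading is not certain.** A reader might infer that existing use would be reported as compensation. The Protocol says only that the question can be examined. What can be said is that the two could not be told apart.
- **Better measurement buys little.** With about 20 quitters, a baseline item will not yield a precise estimate, and setting quitters beside continuing smokers conditions on the trial's outcome. Both parts stand. They are reasons to report use by randomised arm in all participants, to keep the other contrast descriptive, and to accept narrowing the sentence as an alternative.

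**Conclusion.** The point holds in a limited form. For e-cigarettes, cigars and smokeless tobacco the Protocol claims to be able to examine compensation, but its listed measures cannot distinguish new use from continued use, and continuing smokers have no equivalent current-use rate. The questions asked of both arms soften this for e-cigarettes and NRT without giving a change from baseline.

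The size of the error depends on prior use of other products, which the documents do not give. Over an assumed 10% to 30%, the item would show that same 10% to 30% with no initiation at all. The count of 18 to 22 abstainers measures who is asked and how imprecise the result will be. It does not measure the bias.

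The conclusion assumes that the listed baseline topics are complete for these products. It is a minor measurement point, and the treatment comparison on abstinence is untouched.

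**What to change.** 1. At baseline and again at 6 months, ask all participants the same short items on current use of each other tobacco or nicotine product (e-cigarettes, cigars, smokeless tobacco, other), including an amount so that an increase can be seen.
2. Define compensation as new or increased use since baseline.
3. Report other-product use by randomised arm in all participants. Treat any contrast of quitters with continuing smokers as descriptive only, and give confidence intervals.
4. If baseline collection is closed, limit the sentence in the follow-up survey description to the prevalence of other-product use among abstainers.

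Items 1 to 3 cost a few questions in two telephone interviews that already take place, slightly longer calls, and a minor ethics amendment. Item 4 is a wording change only.

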conditions to be offered versus not offered Nicotine Patches. A randomized half of the eligible participants will be assigned to the experimental condition and asked for their permission to have Nicotine Patches sent to their home. The 6-month follow-up survey will be conducted 6-months after the baseline survey. A letter will be sent to the participant in the 2 weeks prior to the telephone survey to notify the participant of its occurrence.

*Randomization:* Interviews will be conducted using computer assisted telephone interview (CATI) technology. At the end of the baseline interview, eligible subjects will be allocated to experimental and control conditions using block randomization (1:1 ratio) built into the CATI program (no stratification or minimization is necessary given the large proposed sample size in this trial).

*Protecting against sources of bias:* The interviewers conducting the baseline and 6-month post-intervention follow-up survey will be blind to experimental condition at the time the key outcome questions are asked. Further, while it is possible that a participant might ‘unblind’ themselves to an interviewer by volunteering that they used the nicotine patch, this is still unlikely to have an impact as the interviewers will be part of a separately contracted telephone survey research firm and will not be aware of the hypotheses of this research trial or be involved in the randomization process.

**Inclusion criteria:** The baseline telephone survey will identify adults (age 18 or over) who smoke 10 or more cigarettes a day, and who are willing to take part in a smoking study that involves two interviews. As part of the baseline survey, all participants will be asked a series of questions to assess their level of interest in receiving free NRT: “The Ministry of Health is considering different ways to help people stop smoking. One option would be to provide interested smokers with free Nicotine Patches. If Nicotine Patches were offered for free, would you be interested in receiving them?” Those who say “yes” will then be asked if they would use the Nicotine Patch to quit smoking. Those who say “yes” to this question will be asked if they would begin to use the Patch within 1 week of receiving it. A “yes” to this question will lead to being asked if they would be willing to have the Patch sent to their home. These items have been employed in our previous research trial of mailed NRT (albeit largely in urban regions).

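### The survey target of 1,252 does not deliver 290 per group: on the protocol's own rates it yields about 282, and 580 randomised would need 1,287

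*Protocol*

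**What the plan says.** All the figures are in the Power calculations paragraph of the protocol, under Measures. The requirement is stated as "A sample of 290 participants per group (intervention versus control) is needed in order to obtain 80% power with 95% confidence interval", for an assumed effect of "OR = 7.1; 6.7% 30-day abstinence rate at 6 months in those receiving NRT vs 1% in those not receiving the intervention". Attrition is already inside the 290: "Randomly distributed dropouts were also included in the simulations, at a rate of 20" per cent. Allocation is 1:1 (Methods, Randomization), so the requirement is 580 randomised.

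The paragraph then works back to the survey. It takes 50.1% of rural respondents as interested in the patches, "leading to a baseline survey needed of 1,138 participants". It next reports that in the earlier trial 10% of people recruited at baseline had a contraindicating health condition. It allows for this by taking 110% of 1,138, and concludes that "we would need to recruit 1,252 participants for the baseline survey".

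**The concern.** The survey target exists only to supply the randomised sample, so it should return 290 per group when the stated rates are applied to it. It does not. The step to 1,138 does not follow from 580 and 50.1%. The step to 1,252 treats a loss expressed as a share of those recruited as if it were a mark-up on those retained. The two slips act in the same direction and compound.

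The survey count is the only recruitment target the protocol gives beyond the 290 per group. If fieldwork is contracted and closed on that count, the trial should expect to miss its stated randomised size. Because 290 was presented as the number that gives 80% power, it may also fall marginally below that power.

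**Working it through.** **Inputs** (all from Power calculations, except the allocation ratio, which is under Randomization): 290 per group; 1:1 allocation; 20% dropout already included; 50.1% interested; 10% of those recruited medically ineligible; 6.7% against 1% abstinent.

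**1. The protocol's own figure.** 1,138 x 1.10 = 1,251.8, which rounds to 1,252. The last operation is reproduced exactly, so the fault lies in the chain and not in that multiplication.

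**2. The interest step.** 2 x 290 = 580, and 580/0.501 = 1,157.7, so 1,158 interviews are needed. In reverse, 1,138 x 0.501 = 570, or 285 per group. The figure 1,138 is also close to 580/0.51 = 1,137.3, so 51% may have been used in place of 50.1%. The text does not show which happened.

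**3. The ineligibility step.** If 10% of those recruited are lost, 90% remain, and the required number is divided by 0.90. Even starting from 1,138, this gives 1,138/0.90 = 1,264.4, so 1,265, not 1,252.

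**4. Both steps corrected.** 580/(0.501 x 0.90) = 1,286.3, so 1,287. The printed target is 1,287 - 1,252 = 35 interviews too low (35/1,287 = 2.7%).

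**5. What 1,252 delivers.**

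| Interest rate | Ineligibility step | Randomised per group |
|---|---|---|
| 50.1% (as stated) | x 0.90 | 1,252 x 0.90 x 0.501 / 2 = 282.3 |
| 51% | x 0.90 | 1,252 x 0.90 x 0.51 / 2 = 287.3 |
| 50.1% | / 1.10 | 1,252 / 1.10 x 0.501 / 2 = 285.1 |
| 51% | / 1.10 | 1,252 / 1.10 x 0.51 / 2 = 290.2 |

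Only the last row, which contains both slips, returns 290. On the stated rates the total is 564.5, a shortfall of 580 - 564.5 = 15.5.

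**6. Effect on power.** The protocol's primary rule counts people lost to follow-up as smokers (Analysis Plan, Step 1). With 20% dropout the expected observed rates are 0.8 x 6.7% = 5.36% and 0.8 x 1% = 0.8%. The power below comes from enumerating all pairs of binomial counts, two-sided at 0.05, ignoring clustering by municipality. For the Wald test, tables with no quitters in a group are counted as non-significant.

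| Per group | Wald test of the log odds ratio | Score (uncorrected chi-square) test |
|---|---|---|
| 290 | 80.9% | 93.3% |
| 285 | 79.9% | 92.9% |
| 282 | 79.3% | 92.7% |

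Analysing completers only gives nearly the same Wald result: 81.0% with 232 completers per group (0.8 x 290) and 79.5% with 226 (0.8 x 282). The Wald test is used as the reference because it reproduces the protocol's 80% at 290. The simple pooled two-proportion formula needs only 178 completers per group, or 223 after dropout.

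**The case against.** The case against giving this much weight is a reasonable one.

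- **Size.** The shortfall is 8 per group, 2.7%, and the Wald power at 282 is 0.7 points below a nominal 80%. This stands.
- **Dependence on the test.** The protocol says only that power was simulated and names no test, so the Wald reading is an inference from the fact that it gives about 80% at 290. Under the score test nothing of practical importance is lost. This stands, and it limits the power consequence, though not the mismatch in numbers.
- **Uncertain inputs.** The 50.1% is an estimate from an earlier trial. An interest rate of 580/(1,252 x 0.90) = 51.5% would be enough for 1,252 to deliver 580, and the realised rate could easily differ from plan by that much. This is true, but it bears on the accuracy of the forecast. The protocol adopts 50.1% and 10%, and its target should follow from them.
- **The 50.1% may already exclude ineligible people.** In that case 1,252 x 0.501 / 2 = 313.6 per group and there is no shortfall. However, the protocol applies the 10% as a further, separate loss, and that step would then be redundant.
- **Recruitment may continue until 580 are randomised.** The protocol does not say that fieldwork stops at 1,252, and it has a back-up recruitment route. Nor does it say that recruitment closes on the number randomised, so the point is open and not answered.

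**Conclusion.** The point holds. On the protocol's stated rates, 1,252 interviews yield 564.5 randomised, about 282 per group, and 580 randomised requires 1,287. The mismatch survives the most favourable reading of the first slip: with 51% interest, 1,252 gives 287 per group. It rests on applying the 50.1% and the 10% one after the other, as the protocol does.

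The consequence is minor. Power falls by about 1.6 points under a Wald logistic test, just enough to cross the stated 80%, and by less than one point, from a much higher level, under a score test. This is an arithmetic error to correct and does not by itself show that the trial is materially underpowered.

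**What to change.** Restate the Power calculations paragraph so that its figures agree, in one of two ways:

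- keep 290 per group and give the survey target as 580/(0.501 x 0.90) = 1,287, with 1,158 as the intermediate figure; or
- keep 1,252 and state that it is expected to yield about 282 per group, with the power at that size and the test it refers to.

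In either case, add a sentence saying that recruitment closes on the number randomised, with the survey count as a planning estimate. That protects the trial against error in the 50.1% and the 10% as well.

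The first option costs 35 more baseline interviews. The second costs only a change of wording. Neither requires a change to the analysis.

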### **Principal research questions**

**Question 1:** Will an intervention of known efficacy – the distribution of free-of-cost nicotine patches sent by postal mail – have a large impact in rural regions of Canada?

**Primary Hypothesis:** Participants receiving the NRT package will display significantly greater quit rates (30 day abstinence) at 6-month follow-up as compared to those not offered the NRT package.

Our analysis plan also includes a test whether **participant gender moderates** the impact of the intervention.

**Question 2:** What other factors that systematically vary between municipalities impact the effectiveness of the nicotine patch intervention? We will use the work of Corsi et al. (2012, 2013), as well as work by co-authors [name] and [name] identifying geospatial factors related to smoking, on the community-level factors related to smoking in Canada to identify relevant factors [prevalence of smoking, availability of health services, average socioeconomic status (SES), population density, region of Canada, tobacco retailer density, NRT distributor density (e.g., pharmacy, grocery store)].

While an extended set of municipal factors listed here will be collected (and examined for their predictive value as part of our secondary analyses), we focus on two contextual factors that we believe are key to why the NRT intervention may be especially impactful in rural settings.

**Prevalence of Smoking Hypothesis:** The impact of the NRT intervention will be larger in municipalities where there is a higher prevalence of smoking compared to municipalities where the prevalence of smoking is lower.

*Smoking is more prevalent in rural regions than in urban regions.* Because of this known higher prevalence of smoking rates in rural versus urban regions, and because the impact of the

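### The primary logistic model is planned for about two or three control quitters, and neither usual maximum-likelihood test from it behaves well there; naming a score or Firth test is a cheap improvement.

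*Protocol*

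**What the plan says.** The Analysis Plan opens with "Multilevel logistic modelling will be employed". In Step 1, randomised condition "is the categorical predictor in these analyses", and "Participants lost to follow-up will be assumed to be current smokers". No estimation method, test statistic or rule for an empty cell is given.

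Power calculations sets the planning effect at "6.7% 30-day abstinence rate at 6 months in those receiving NRT vs 1% in those not receiving the intervention" (OR 7.1) and concludes: "A sample of 290 participants per group (intervention versus control) is needed in order to obtain 80% power with 95% confidence interval". The method is Monte Carlo simulation with 20% random dropout; the test applied to each simulated trial is not stated.

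Allocation is by individual, 1:1, under Randomization.

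**The concern.** A 1% control rate in 290 people leaves very few events in that arm. When an arm has no events, the logistic likelihood keeps rising as the log odds ratio goes to infinity. There is then no finite estimate, and the Wald standard error explodes. A random intercept for municipality does not help: whatever its variance, the likelihood still rises as the control log-odds fall.

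With counts this small, the choice between the tests that a logistic fit usually offers also changes the power and the false-positive rate considerably. At stake are a usable primary odds ratio and interval, power that the sample already contains, and control of the type I error.

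**Working it through.** **Inputs (Power calculations; Analysis Plan, Step 1).** 290 per group; 6.7% vs 1%; 20% dropout; dropouts counted as smokers. I read the 95% confidence interval as a two-sided 5% test. The documents do not settle whether the 1% applies before or after counting dropouts as smokers, so both readings are shown.

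- Reading A (rates apply to those followed up): 0.8 × 6.7% = 5.36% vs 0.8 × 1% = 0.8%.
- Reading B (rates already count dropouts as smokers): 6.7% vs 1%.

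**The plan's own figures.** OR = (0.067/0.933)/(0.01/0.99) = 7.11, which agrees with the stated 7.1. Enumerating all 2×2 tables under reading A, with an empty cell counted as a Wald non-rejection, the ordinary logistic Wald test needs 286 per group for 80% power and has 80.9% at 290. Closed-form two-proportion formulas give 178/0.8 = 223 per group, or 212/0.8 = 265 with continuity correction. So 290 is consistent with a Wald-based simulation.

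**Expected control quitters and the chance of none.**

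- A: 290 × 0.008 = 2.32; 0.992^290 = 9.7%. (Patch arm: 290 × 0.0536 = 15.5.)
- B: 290 × 0.01 = 2.9; 0.99^290 = 5.4%. (Patch arm: 290 × 0.067 = 19.4.)

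**What an empty control arm does.** For 16/290 vs 0/290, a maximum-likelihood logistic fit returns a log OR of 22.7 with a standard error of about 12,700 and Wald p = 0.999. On the same table the likelihood-ratio p is 2 × 10⁻⁶ and the Fisher p is 2.5 × 10⁻⁵.

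**Operating characteristics at 290 per group.** Exact enumeration, single-level, two-sided 5%. Type I error is computed with both arms at the control rate (0.8% for A, 1% for B).

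| Test | Power A | Power B | Type I error A | Type I error B |
|---|---|---|---|---|
| Logistic Wald | 80.9% | 91.0% | 0.13% | 0.35% |
| Logistic likelihood ratio | 93.8% | 97.4% | 9.5% | 8.8% |
| Pearson chi-square (score) | 93.4% | 97.3% | 4.5% | 4.6% |
| Firth penalised likelihood ratio | 92.6% | 97.2% | 2.1% | 2.9% |

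The likelihood-ratio test is liberal because very small splits count as significant. For 3 quitters vs 0 the statistic is about 2 × 3 × ln 2 = 4.16, above the 3.84 cut-off. The Pearson statistic for the same table is 580 × 3/577 = 3.02, below it.

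Under reading A the Wald test gives up 93.4 − 80.9 = 12.5 points of power against the score test. Trials with no control quitter make up about 9.7 of the 100 − 80.9 = 19.1 points that it misses.

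**The case against.** The strongest reply is that the protocol names neither maximum likelihood nor a Wald test, and that the choice of test and an empty-cell rule are usually left to the SAP, which is not shown. This stands in part. The protocol cannot be said to have chosen a failing test, and a likelihood-ratio test from the same model would detect the effect in more than 99.9% of trials with no control quitter. But that test has a type I error of about 9%. The point is therefore not a missing detail: the protocol fixes the model class and the planning rates, and neither usual maximum-likelihood test suits the two together.

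Three stronger readings are tempting, and the documents do not support them.

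- *The trial is underpowered, or its 80% is wrong.* It is not. Even the Wald test reaches 80.9% with empty-cell trials counted as failures, and its error is on the conservative side.
- *The 290 proves a Wald analysis.* The interval reported for the earlier rural subgroup (OR 9.59, 1.19 to 77.16, n = 200) is of Wald type: 9/101 vs 1/99 reproduces it exactly. That shows past practice, not the plan for this trial. Nor is 290 unique to the plain Wald test. A Wald test with 0.5 added to each cell has about 80% power at 232 per group under the reading A rates, and 232/0.8 = 290 if dropout is counted twice.
- *The gender moderation test fails more often still.* With an assumed equal gender split and rural controls alone (116 followed up per gender at 1%), the chance of at least one empty control cell would be 1 − (1 − 0.99^116)² = 53%. But the Analysis Plan places gender in Step 2, on data pooled with the urban sample, so that figure does not describe the planned model.

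**Conclusion.** The point holds as an improvement to the primary analysis, not as an error in the sample size. At the protocol's own rates there is a 5% to 10% chance that a maximum-likelihood logistic model gives no finite odds ratio. A Wald test would then forgo about 12 points of power under reading A (6 under reading B), while a likelihood-ratio test would nearly double the nominal error rate.

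This rests on a true control rate near 1%, a two-sided 5% level and single-level enumeration; no multilevel model was simulated. A higher control quit rate would shrink the problem. The biochemically validated replication in Step 1 can only have as many events or fewer, so the problem there is at least as large.

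**What to change.** In Step 1 of the Analysis Plan, name one primary test of condition: the Pearson chi-square (score) test or the Firth penalised likelihood-ratio test. Report the odds ratio from a Firth fit with a profile-penalised confidence interval, and the risk difference with a score-type interval. Keep the multilevel logistic model as a supportive analysis; since allocation is by individual, the primary comparison does not need the municipality effect. In Power calculations, state which test the 80% refers to. With either proposed test, 290 per group gives about 93% at the planned rates.

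The cost is wording only, with no extra participants or data, and it should be settled before outcome data are seen by condition. The one downside is that the municipality random effect leaves the primary test.
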